## 6.2 Definition of study populations

All efficacy and safety analyses will be conducted on the all Treated population which will comprise all randomized patients receiving study treatment.

Patients will be included in the groups to which they were randomized for all evaluations of efficacy and in the groups according to treatment received for all evaluations of safety.

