#### 4.3.3 Withdrawal of patients from treatment or study

##### 4.3.3.1 *Withdrawal from treatment*

A patient should be withdrawn from the study treatment if, in the opinion of the Investigator, it is medically necessary, or if it is the wish of the patient.

When a patient is withdrawn, the date of last IMP (investigational medicinal products) administration and the date and reason for treatment withdrawal should be clearly described in the relevant sections of the CRF. If a patient is removed from treatment because of an AE, the reason for treatment withdrawal should always be stated as 'adverse event' irrespective of whether this was the investigator's or the patient's decision.

If a patient withdraws due to worsening of disease, patient should be treated as a non-responder. In these case, the patient will be able to receive treatments that are protocolized at their hospital. The patient could be treated with pulses of steroids, intravenous immunoglobulins, betainterferon and other biologic or immunosuppressants agents such as cyclosporin, tacrolimus, baricitinib, tocilizumab, sarilumab, ruxolitinib...

The patient will continue to participate in the study without taking study treatment.

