## 4.4 Treatments

### 4.4.1 Treatments administered

According to the randomization schedule, patients in arm A will receive (IMP) and standard of care and patients in arm B will receive standard of care only, see Table 1.

The treatment standard of care will be based on hydroxychloroquine and/or lopinavir-ritonavir and/or azithromycin.

Table 1:

| Arm | Investigational product | Dosage form | Route         | Daily dose                                                                                           | Dosage regimen              |
|-----|-------------------------|-------------|---------------|------------------------------------------------------------------------------------------------------|-----------------------------|
| A   | Anakinra                | Solution    | i.v. infusion | Days 1-15: 400 mg/day in total, divided into 4 doses given every 6 hours                             | 4 times daily for 15 days   |
| A   | Hydroxychloroquine      | Tablets     | Oral          | Day 1-15: 400 mg/day in total, divided into 2 doses given every 12 hours (loading dose: 400 mg/12 h) | 2 times daily for 5 days    |
| A   | Lopinavir-Ritonavir     | Tablets     | Oral          | Day 1-15: 800/200 mg/day in total, divided into 2 doses given every 12 h                             | 2 times daily for 5-7 days. |
| A   | Azithromycin            | Tablets     | Oral          | Day 1-15: 500 mg /day                                                                                | 1 time daily for 5 days.    |
| B   | Hydroxychloroquine      | Tablets     | Oral          | Day 1-15: 400 mg/day in total, divided into 2 doses given every 12 hours (loading dose: 400 mg/12 h) | 2 times daily for 5 days    |
| B   | Lopinavir-Ritonavir     | Tablets     | Oral          | Day 1-15: 800/200 mg/day in total, divided into 2 doses given every 12 hours                         | 2 times daily for 5-7 days. |
| B   | Azithromycin            | Tablets     | Oral          | Day 1-15: 500 mg /day                                                                                | 1 time daily for 5 days.    |

---

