#### 4.4.6 Blinding and unblinding

This is an open study with no level of blinding.

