### 6.3.3 Analysis related to primary objective

#### *6.3.3.1 Primary endpoint*

##### Treatment success

The main outcome variable is the percentage of patients requiring mechanical ventilation at 15 days after the start of treatment. The comparison of these proportions would be done by chi-square test, with significance level 0.05 and presentation in the form of absolute risk

reduction, relative risk reduction and number needed to treat, with their respective 95% confidence intervals.

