#### *6.3.3.2 Secondary endpoints supporting the primary objective*

##### Time to mechanical ventilation

Analysis of the time to mechanical ventilation from the point of randomization will be undertaken by plotting Kaplan-Meier curves for each of the 2 treatment groups and by pairwise comparisons (anakinra versus standard of care) using the log rank test. Hazard ratios will be estimated using the Cox proportional hazards model and these will be presented together with 90% two-sided confidence intervals.

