#### 6.3.8 Handling of missing data

There will be no computation of missing data.

---

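### Efficacy is analysed only in randomised patients who receive study treatment, so in this open-label trial exclusion can depend on the arm; the time origin and unknown Day-15 outcomes also need a single rule

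*Protocol*

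**What the plan says.** **Analysis set.** Protocol Section 6.2 fixes one set for everything: "All efficacy and safety analyses will be conducted on the all Treated population which will comprise all randomized patients receiving study treatment". Within that set, "Patients will be included in the groups to which they were randomized for all evaluations of efficacy". No all-randomised set is named. Section 4.4.1 says that "patients in arm B will receive standard of care only", and Section 4.4.6 says "This is an open study with no level of blinding". Under Section 4.4.3 the allocation is passed back to the staff who deliver the intervention, so it is known before dosing. Section 4.5.1.3 places randomisation and the first dose at the same visit, Day 1.

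**Time origin.** Section 6.3.3.1 defines the main outcome as the percentage of patients "requiring mechanical ventilation at 15 days after the start of treatment", and Section 6.3.4.1 dates the Day-28 proportion in the same way. Section 6.3.3.2 instead plans "Analysis of the time to mechanical ventilation from the point of randomization", and time in ICU and in hospital is also counted from randomisation.

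**Missing outcomes.** Section 6.3.8 says "There will be no computation of missing data". Sections 4.3.3.1 and 4.4.9 add one outcome rule: "If a patient withdraws due to worsening of disease, patient should be treated as a non-responder". Section 4.3.3.1 then keeps a patient who has stopped treatment in the study, whereas Section 4.4.9 takes patients who need biological drugs out of it.

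**The concern.** Randomisation protects the comparison only for the set of patients who were randomised. Once staff and patient know the arm, whether treatment ever starts can depend on the arm and on the patient's course, and Section 6.2 makes starting treatment a condition for being counted.

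The condition does not bite equally. If study treatment meant the investigational drug, arm B would have no analysable patients, so for arm B it must mean standard of care. That is usual hospital treatment, and the condition is easily met. In arm A there is an additional drug that a patient can refuse or become too ill to start. Someone who is intubated before the first infusion can drop out of arm A, while the same patient in arm B counts as a failure.

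Failures are few by assumption, so a handful of selective exclusions or unknown outcomes matters. Section 6.1 says convincing results may be used to seek regulatory approvals, and Section 6.3.1 claims 5% type I error control. The two time origins and the missing counting rule add avoidable ambiguity about which patients and which days make up the Day-15 proportion.

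**Working it through.** **Inputs (Section 6.1):** 90 patients per arm; success 88% on standard of care and 92% on anakinra; 10% loss. The 12% failure rate is 100% - 88%. The number of patients never dosed is not given, so step 2 uses assumed values.

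**1. Planned effect in patients.** Expected failures: 0.12 × 90 = 10.8 in arm B and 0.08 × 90 = 7.2 in arm A. The difference is 3.6 patients, or 4 points. (The stated assumptions do not reproduce 90 per arm. That is a separate matter and does not bear on this point.)

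**2. Bias from the treated-only set.** Assume no true effect, 12% failures in both arms, and k excluded patients who are all arm A failures. The apparent benefit is 0.12 - (10.8 - k)/(90 - k).

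| k | Arm A failure rate | False benefit (points) |
|---|---|---|
| 1 | 9.8/89 = 11.0% | 1.0 |
| 2 | 8.8/88 = 10.0% | 2.0 |
| 3 | 7.8/87 = 9.0% | 3.0 |
| 4 | 6.8/86 = 7.9% | 4.1 |

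With the 15% ventilation rate that Section 6.1 takes from the hospital database, k = 4 gives 0.15 - 9.5/86 = 3.95 points, about the same.

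**3. Effect on the test.** In a simulation of 200,000 trials per setting (two-sided pooled test, no true effect, 12% failures), a given share of arm A failures was dropped:

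| Share of arm A failures dropped | Type I error |
|---|---|
| 0% | 5.0% |
| 10% (about 1 patient) | 5.6% |
| 20% (about 2) | 7.3% |
| 30% (about 3) | 10.9% |

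**4. Unknown Day-15 outcomes.** Assume the full 10% allowance is unknown: 0.10 × 90 = 9 per arm, leaving 81 observed. At the planned rates, observed successes are 0.92 × 81 = 74.52 (arm A) and 0.88 × 81 = 71.28 (arm B). The difference over all 90 per arm is then:
- unknowns all fail in A and all succeed in B: (74.52 - 80.28)/90 = -6.4 points;
- unknowns all succeed in A and all fail in B: (83.52 - 71.28)/90 = +13.6 points;
- unknowns fail in both arms: (74.52 - 71.28)/90 = +3.6 points.

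**5. Power cost of the full set.** At 88% against 92%, two-sided power is 14.3% with 90 per arm and 13.3% with 81. At fixed rates, counting everyone loses no power.

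**6. Time origin.** Tables 1 and 3 and Section 4.5.1.3 put randomisation and treatment on the same Day 1. If that schedule is kept, the two origins coincide. They separate when a first dose is delayed, and a patient never dosed has no origin at all for the ventilation proportions.

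**The case against.** The strongest reply is that little may be lost in practice. The first dose is due at the randomisation visit, so never-dosed patients may be very few, and those who are dosed are analysed as randomised. Both facts stand and limit the likely size of the bias. They do not remove the rule that permits it.

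The illustration is also one-sided by construction: every excluded patient is an arm A failure. Exclusions unrelated to outcome would cause no such bias. Nor should it be inferred that four patients decide the result. The planned gap is far from significance anyway: 7/90 against 11/90 gives p of about 0.32 by uncorrected chi-square. Four selective exclusions can equal the planned effect; they do not settle the test.

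A reader might infer three stronger things that the protocol does not support:
- *That the clock starts earlier in arm B because standard of care was already running.* No section says so, and Table 1 lists arm B treatment from Day 1, as for arm A. What remains is inconsistent wording.
- *That missing outcomes are not handled at all.* Withdrawal for worsening counts as non-response, Section 4.1 plans follow-up by telephone or in person to the end of the study, and Section 4.5.1.6 allows Day 28 by telephone. The gap concerns other unknown outcomes.
- *That the 10% loss is the share never dosed.* It is a sample-size allowance; step 4 uses it only as an assumed number of unknowns.

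Further missing-data detail may be in a statistical analysis plan that was not available. That plan would not be expected to reverse a population the protocol fixes explicitly.

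**Conclusion.** The point holds in a limited form. Section 6.2 exposes the primary comparison to exclusions that depend on the assigned arm, and analysis by randomised group does not repair that. It would be too strong to say that the randomised comparison is broken: that depends on how many patients go undosed and why, which the protocol does not state.

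If exclusions are confined to arm A failures, four of 90 give a false benefit of about 4.1 points, matching the planned 4. If all nine allowed losses per arm were unknown outcomes, the all-randomised difference could lie between -6.4 and +13.6 points; that range gives the extremes and does not forecast the result. The two time origins are a real inconsistency, but on the planned schedule a minor one. The disagreement between Sections 4.3.3.1 and 4.4.9 matters more, because it concerns patients who are worsening and whose outcomes are the most informative.

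**What to change.** - Make the primary efficacy set all randomised patients in their assigned arm. Keep the treated set for safety only, and define there what study treatment means in arm B.
- Use randomisation as time zero for every efficacy endpoint, including the Day-15 and Day-28 ventilation proportions.
- Count Day-15 and Day-28 status for everyone randomised, including patients never dosed or off treatment, through the follow-up already planned in Sections 4.1, 4.3.3.1 and 4.5.1.6. Ask about ventilation at the Day-28 contact, since Section 4.5.3.1 schedules that assessment only at Visits 1 to 4.
- State how an unknown Day-15 status is counted, and report best-case and worst-case bounds for any that remain unknown.
- Reconcile Section 4.3.3.1 (patient stays in the study) with Section 4.4.9 (patient needing biological drugs is removed), so that outcome follow-up is not lost.

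The cost is revised wording, a little more analysis work, and slight dilution of the effect if some patients are never dosed.

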## 6.3 Overall statistical and analytical plan

Statistical analysis will be performed using PASW 21.0 statistical package.

### 6.3.1 General statistical issues

This design has acceptable properties in terms of the false positive potential, controlling the overall type I error at 5%, for each of the two treatment comparisons.

Secondary endpoints will be evaluated in a descriptive way. In some cases, p-value comparisons will be undertaken, but these are to be interpreted in an exploratory way.

### 6.3.2 Demographics and baseline characteristics

Demographic and baseline characteristics will be summarized in appropriate tabular presentations.

For measurements of continuous endpoints, summary statistics will include n, mean, median, standard deviation, minimum and maximum values. For categorical variables, summary tabulations of the number and percentage within each category (with a category for missing data) of the parameter will be presented.

### 6.3.3 Analysis related to primary objective

#### *6.3.3.1 Primary endpoint*

##### Treatment success

The main outcome variable is the percentage of patients requiring mechanical ventilation at 15 days after the start of treatment. The comparison of these proportions would be done by chi-square test, with significance level 0.05 and presentation in the form of absolute risk

reduction, relative risk reduction and number needed to treat, with their respective 95% confidence intervals.

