#### 4.4.3 Method of assigning patients to treatment groups

The different treatment groups are;

- Arm A: Anakinra as add-on to standard of care
- Arm B: Standard of care only

The ratio between the treatment groups is 1:1, i.e., the same number of patients will be randomized to anakinra or standard of care.

In order to assign each patient to each of the treatment branches and ensure a balance between them for the different centers, the method of random allocation by permuted blocks of sizes 10 and 12 will be used, using the randomizer library of the R statistical package, version 3.4.0.

Although the study is open, measures are taken to prevent a selection bias: one collaborator from each center will be in charge of the allocation, for which he will receive the identifying information of each recruited subject (trial identification number), attaching the branch indicated by the random procedure and returning this information to the people in charge of continuing the development of the intervention.

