##### *4.5.3.2 MEWS score*

Modified early warning system score (MEWS) will be assessed at Day 1 and Day 15 and recorded in the CRF if ICU is needed.

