##### *4.5.3.3 SpO2*

Resting peripheral capillary oxygen saturation (SpO2) will be measured 3 times per day by pulse oxymetry at Visits 1 to 4 and recorded in the CRF. Saturation normalization will be measured, both as an absolute value and as a relative value with respect to the baseline situation of income.

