## 6 Statistical plan

### 6.1 Determination of sample size

The study will enroll a total of 180 patients, 90 per arm according to the 1:1 randomization. The sample size has been estimated based on the following assumptions:

- The sample size is calculated in based of the data collected in the database of COVID-19 of the Complejo Hospitalario de Navarra , which currently has a total of 188 patients. After the analysis of the data, it is estimated that 15% of severe pneumonia COVID patients have required mechanical ventilation.
- For and Type I error of 0.05 and a power of 75% for each comparison under the assumption that the true success rates are 88% in the SoC group increasing to 92% in the anakinra group.
- It is needed 180 patients (90 per arm) considering a loss of 10%.
- The study will consist of two stages, with equal numbers of patients randomised into Stage 1 (treatment) and into Stage 2 (follow-up) per treatment arm.

The calculations on the operating characteristics of this design have been undertaken using the website of Sample size calculator of *National Center for Advancing Translational Sciences, National Institutes of Health*, through [UCSF-CTSI](#) , Software utilities developed by [[contact]](mailto:[contact]), last up to date version on April 14, 2020.

The value for the type I error has been chosen in recognition of the urgent unmet medical need to allow the identification of a signal, at least, from a statistical perspective. Having seen a statistical signal, it is then a matter of evaluating whether the observed treatment differences represent clinically relevant effects that can satisfy that unmet need.

In case indications of efficacy requires to be confirmed, additional patients may be added into this study.

In case the outcome is statistically convincing, efficacy will be considered confirmed and the results will, where warranted, be used to seek regulatory approvals.

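### The primary chi-square leaves out baseline oxygenation, although screening PaO2/FiO2 is scheduled for every patient; some precision is lost, but the test is valid

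*Protocol*

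**What the plan says.** Section 6.3.3.1 compares the proportions ventilated at 15 days: "The comparison of these proportions would be done by chi-square test, with significance level 0.05". Results are to be shown as absolute and relative risk reduction and number needed to treat, each with a 95% interval. No covariate or stratification factor is named there, and no other section adds an adjusted analysis of this endpoint.

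Allocation (section 4.4.3) uses permuted blocks of 10 and 12 to "ensure a balance between them for the different centers". Respiratory severity plays no part in it.

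Baseline oxygenation is on the schedule. Table 3 (section 4.5.1.1) has PaO2/FiO2 at screening, and section 6.3.3.2 takes the screening value as the baseline for change in PaO2/FiO2. Resting SpO2 "will be measured 3 times per day by pulse oxymetry at Visits 1 to 4 and recorded in the CRF", and Visit 1 is Day 1. The Day 1 MEWS score, by contrast, is "recorded in the CRF if ICU is needed".

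Section 6.1 plans for "a power of 75% for each comparison under the assumption that the true success rates are 88% in the SoC group increasing to 92" per cent, and states: "It is needed 180 patients (90 per arm) considering a loss of 10" per cent.

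**The concern.** The endpoint is progression to mechanical ventilation. Section 4.3.1 admits patients with ambient saturation of 94% or less, or Pa:FiO2 of 300 or less, with no lower limit short of the intubation exclusion in section 4.3.2. It is reasonable to expect oxygenation at entry to predict who is ventilated, though the protocol does not quantify this.

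Neither the allocation nor the analysis uses that information. With about 16 ventilated patients expected, one arm can by chance draw the sicker patients, and the unadjusted risk difference and number needed to treat will carry that imbalance. A prespecified adjustment removes most of it using data already scheduled. Chosen after the data are seen, in an open-label trial, the same adjustment would have little credibility.

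**Working it through.** **Inputs from the protocol.** Success 88% versus 92%, so ventilation 12% versus 8%. Enrolment of 90 per arm with 10% loss gives 90 × 0.9 = 81 evaluable per arm, 162 in all. Allocation 1:1. Chi-square at 0.05, two-sided in effect. Expected events: 81 × 0.12 + 81 × 0.08 = 16.2.

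**The plan's own figure.** Sample size per arm for two proportions (pooled variance under the null):

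n = [1.96 × √(2 × 0.90 × 0.10) + 0.6745 × √(0.88 × 0.12 + 0.92 × 0.08)]² / 0.04² = (0.8316 + 0.2855)² / 0.0016 ≈ 780.

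The stated 90 per arm for 75% power does not reproduce. Power at n per arm is Φ[(0.04√n − 0.8316) / 0.4233]: 14.3% at 90 and 13.3% at 81. The 13.3% is the base on which adjustment acts.

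**Current precision.** SE of the risk difference = √[(0.12 × 0.88 + 0.08 × 0.92) / 81] = √0.002212 = 0.0470, a 95% half-width of about 9.2 percentage points.

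**Effect of adjustment.** This depends on the prognostic strength of baseline oxygenation, which the protocol does not give. The range of odds ratios per SD below is assumed. Two simulations at 81 per arm and 12% versus 8% compared the unadjusted risk difference with one standardised from a logistic model containing treatment and one baseline covariate. The last column puts n = 81 / (variance ratio) from simulation B into the power formula.

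| Assumed odds ratio per SD | Variance ratio, A (4,000 runs) | Variance ratio, B | Power implied by B |
|---|---|---|---|
| 1.5 | 0.985 | 0.99 | 13.4% |
| 2 | 0.963 | 0.94 | 13.8% |
| 3 | 0.916 | 0.90 | 14.3% |
| 4 | 0.867 | 0.83 | 15.1% |

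The variance falls by about 1–17%. The half-width of 9.2 points becomes 9.2 × √0.99 ≈ 9.2 at one end and 9.2 × √0.83 ≈ 8.4 at the other. Simulated power in A rose from 12.6–12.8% to 13.4–14.8%. Under no effect (12% in both arms), the adjusted test rejected in 4.7–5.2% of runs and the chi-square in 4.4–5.2%. If the covariate is not prognostic, the variance ratio is about 1.01.

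**Chance imbalance.** The difference in covariate means between arms has SE √(2/81) = 0.157 SD. An imbalance above 0.2 SD in either direction therefore has probability 2 × Φ(−0.2/0.157) ≈ 20%. In simulation with odds ratios of 2 to 4 per SD, a 0.2 SD imbalance moves the unadjusted risk difference by about 1.3–2.1 points, one third to one half of the planned 4-point effect. After adjustment the shift is about 0.2 points or less.

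**The case against.** The strongest reply is that nothing in section 6.3.3.1 is wrong. A chi-square in a 1:1 randomised trial holds its level, and the 5% level and 95% interval already allow for chance imbalance on average over randomisations. That stands: this is an efficiency point, not a correction of bias.

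The prognostic strength is also assumed. At odds ratios of 1.5–2 per SD the variance falls by only about 1–6%, and entry criteria cut the range of oxygenation at both ends. That stands too, and is why the size is given as a range.

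A third reply is that the baseline value may be missing. Section 4.3.1 accepts any one of three oxygenation measures, so availability for every patient rests on the visit schedule, not on eligibility. Section 6.3.8 rules out imputation, so a missing covariate could remove a patient from the primary analysis. This is a fair objection to careless adjustment, and the fix must deal with it.

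Two stronger readings are tempting. Because allocation aims to balance centres, a reader might infer that ignoring centre also throws precision away. The figures do not support this. With 5–20 assumed centres, a centre-stratified Cochran-Mantel-Haenszel test changed power by −0.6 to +1.6 points, and the chi-square's size stayed at 3.7–5.4%. The number of centres is not given, and about 16 events would leave many centres with none. A reader might also expect a large power gain by assuming a bigger treatment effect. The protocol plans 88% versus 92%, and at those rates the gain is at most about 2 points.

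**Conclusion.** The point holds as a modest improvement worth making before any data are seen. The primary test is valid but ignores a pre-randomisation measure that the protocol schedules for all patients. Adjustment would reduce the variance of the risk difference by about 1–17% and limit the effect of a chance severity imbalance. It would add about 0–2 points to a power of about 13%. These figures rest on an assumed odds ratio of 1.5–4 per SD, 81 evaluable patients per arm and the protocol's own event rates. Adjustment does not repair the sample size, which is a separate and larger problem.

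Screening PaO2/FiO2 is the covariate to use. Sa:FiO2 is an eligibility criterion but not a Table 3 item. Day 1 SpO2 is read three times on the day of the first dose, and section 4.5.1.3 only prefers assessments before dosing, so some readings may follow treatment. MEWS is recorded only for patients who need ICU.

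**What to change.** In section 6.3.3.1:

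- Make the primary analysis a penalised-likelihood logistic model (events are few) with treatment and one named covariate, screening PaO2/FiO2.
- Report the standardised risk difference with a 95% CI and state the interval method. Relative risk reduction and number needed to treat can come from the same two standardised risks.
- State that a missing baseline PaO2/FiO2 is filled by a simple rule that ignores treatment arm, such as the mean over both arms. Note in section 6.3.8 that its rule against imputation does not apply to this baseline covariate.
- Keep the unadjusted chi-square as a sensitivity analysis.

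The cost is a few sentences, slightly more analysis work and about 1% more variance if the covariate proves non-prognostic. No extra patients or new measurements are needed. Section 6.3 names PASW 21.0, so the sponsor should confirm that it can fit this model or name another package.
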